### 2.10 Randomization and allocation concealment

A third party other than the researchers and evaluators uses a software package to generate random numbers and groups, and compiles and keeps random allocation cards, which are placed in sealed opaque envelopes in sequence. Qualified subjects open the random envelopes with corresponding numbers in the order of inclusion in the trial. In this way, the subjects are randomly divided into the treatment group and the control group, and the operation is carried out strictly according to the grouping in the envelopes.

### 2.11 Assignment of interventions: blinding

Blinding of participants was not feasible in this trial due to the inherent sensory characteristics of moxibustion (e.g., visible smoke, distinct thermal sensation, and herb aroma). To mitigate potential bias arising from participants’ awareness of treatment allocation, outcome assessors, data entry personnel, and statisticians will be blinded to group allocation throughout the study. In addition to patient-reported outcomes, we incorporated objective biomarkers (e.g., ANP and AVP) as secondary endpoints to reduce reliance on subjective assessments. Meanwhile, practitioners delivered a neutral script to all participants before treatment, “This study aims to compare different approaches to managing your condition. Some treatments may produce physical sensations, but we ask you to focus on reporting your symptoms as accurately as possible, regardless of your expectations.”

### 2.12 Data collection and analysis

The data of various observation indicators of patients were collected on the day of treatment, the day after the end of treatment and 2 months after the end of treatment. To ensure the accuracy and completeness of the data, we will adopt a double-entry method. PASW Statistics 18.0 software was used to establish a database for case investigation data that met the inclusion criteria, and data review was performed after data entry was completed.

The statistical analysis of the PASW Statistics 18.0 data was performed, encompassing descriptive statistics for clinical baseline data. For continuous outcomes, group differences will be analyzed using Student’s *t*-tests if data are normally distributed; otherwise, the Mann-Whitney U test will be applied. For categorical variables, Chi-square tests or Fisher’s exact tests will be used as appropriate. Efficacy evaluations utilized both intention-to-treat (ITT) and per-protocol (PP) populations, while safety assessments were conducted on the safety analysis set. In the intention-to-treat analysis, missing data due to withdrawal or dropout will be handled using the last observation carried forward (LOCF) method. Participants who received prohibited therapies were retained in the trial per the ITT principle but flagged for sensitivity analysis. Their data were analyzed both within the full cohort and in a subgroup excluding protocol violators. When necessary, multiple imputation methods will be considered for missing value replacement, or alternative approaches will be selected based on actual circumstances. For clustering, the K-MEANS clustering method was utilized, while applying Pearson or Spearman correlation analysis to examine correlations. A *P*-value of 0.05 or less was considered statistically significant.

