**Method:**

This study is designed as a randomized, single-blind clinical trial, focusing on a population of 110 patients aged 60 and above who suffer from non-specific nocturia lasting for at least 1 month. Patients in the intervention arm are scheduled for 2 cycles of HSM, while patients in the control group will undergo the same cycle of conventional treatment. To ensure objectivity, assessors and investigators will remain blinded to the randomization process. The primary outcome of this study is the reduction in the frequency of nocturia. Additionally, several secondary outcomes will be evaluated, including sleep quality, quality of life scores, the efficacy of traditional Chinese medicine (TCM) syndrome, and changes in blood biomarkers Arginine vasopressin (AVP) and Atrial natriuretic peptide (ANP). These assessments will be conducted at baseline, post-intervention and at the 2-month follow-up to comprehensively evaluate the effectiveness and safety of HSM.

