### 2.7 Procedure

Prior to the commencement of therapy, the practitioner ought to document the patient’s nocturia frequency, administer and record the Pittsburgh Sleep Quality Index (PSQI) and Nocturia Quality of Life (N-QOL) scale scores, assess the traditional Chinese medicine syndrome score, and evaluate the intensity of nocturia and urinary frequency. Upon the morning subsequent to enrollment, fasting blood samples will be procured for the assessment of AVP and ANP levels. Throughout the treatment period, nocturia frequency will be meticulously recorded on a daily basis.

Upon completion of the treatment regimen, the PSQI, N-QOL scale scores, and traditional Chinese medicine syndrome score will be reassessed, and fasting blood samples will be collected the subsequent morning for a repeat analysis of AVP and ANP. Additionally, 2 months post-treatment, these assessments–including the PSQI, N-QOL scale scores, traditional Chinese medicine syndrome score, and fasting blood tests for AVP and ANP–will be conducted once more.

Ultimately, a comprehensive evaluation will encompass the nocturia frequency, sleep quality, quality of life, traditional Chinese medicine syndrome scores, as well as AVP and ANP levels, for both patient cohorts, both pre- and post-treatment, with a further assessment conducted 2 months after the conclusion of therapy. Figure 1 illustrates the clinical procedures during the research.

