### 2.8 Outcome measures

#### 2.8.1 Primary outcomes

The frequency of nocturia: 72-hour urination diary.

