### 2.9 Sample size

Based on relevant research (significance level, take α = 0.05, β = 0.10, test power 1-β = 0.90; two-sided test, confidence level 95%, *Z* = 1.96, *E* = 10%, *P* = 0.5), the estimated sample size is 96 cases preliminary. If the dropout rate is considered to be at most 15%, the total number of cases in the two groups should be at least 110. Therefore, 55 participants were recruited in each group.

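### The primary comparison is not baseline-adjusted, and the protocol does not fix whether it tests post-treatment nocturia frequency or its reduction from baseline

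*Protocol article*

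**What the plan says.** Section 2.12 gives one rule for all continuous outcomes: Student's t-test "if data are normally distributed; otherwise, the Mann-Whitney U test will be applied". It names no covariate and no baseline-adjusted or repeated-measures model for the group comparison. Baseline data appear there only in a descriptive role ("encompassing descriptive statistics for clinical baseline data"). No normality test or threshold is stated.

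The primary outcome is worded in two ways:

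- Abstract, Method: "The primary outcome of this study is the reduction in the frequency of nocturia".
- Section 2.8.1: "The frequency of nocturia: 72-hour urination diary".

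The baseline value is collected. Section 2.7 says that before therapy "the practitioner ought to document the patient’s nocturia frequency", and Table 1 marks nocturia frequency at Week 0, Week 3 and Week 10. The same three time points are marked for PSQI, N-QOL, the TCM syndrome score, AVP and ANP. The Abstract agrees: "These assessments will be conducted at baseline, post-intervention and at the 2-month follow-up".

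**The concern.** Two things are left open that together decide what the primary analysis estimates.

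First, the variable. A post-treatment frequency and a reduction from baseline have different variances unless the baseline correlation is exactly 0.5, so the power of the trial depends on which is meant.

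Second, the test. The t-test addresses a difference in mean voids per night. Mann-Whitney addresses whether values in one arm tend to exceed those in the other. Under section 2.12 the observed distribution decides between them. A mean over a 72-hour diary moves in steps of one third of a void and cannot fall below zero, so non-normality is a realistic result.

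Under every one of these options the Week 0 count does not enter as a covariate. It is likely to be the best available predictor of the later count. Section 2.10 describes no stratification, so a chance difference between arms in baseline nocturia would not be corrected in the analysis.

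**Working it through.** **The plan's own figure.** Section 2.9 gives Z = 1.96, P = 0.5 and E = 10%. The single-proportion precision formula Z²P(1−P)/E² gives 1.96² × 0.25 / 0.01 = 96.04, the stated 96. Then 96 × 1.15 = 110.4, the stated 110. The figure reproduces, but it uses no treatment difference, SD or baseline correlation, so the stated 90% power cannot be carried over to the t-test or the Mann-Whitney test. I use 96/2 = 48 per arm below.

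**Relative variance of the group difference** (post-value t-test = 1, equal SDs before and after, r = correlation of baseline with follow-up):

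- change score: 2(1 − r)
- ANCOVA: 1 − r²
- ANCOVA relative to change score: (1 − r²)/[2(1 − r)] = (1 + r)/2

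ANCOVA is therefore never less precise than either version in large samples. A change score is worse than ignoring baseline when r is below 0.5.

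**Power illustration.** The documents give no effect size, SD or r, so a difference of 0.5 SD and the values of r are my assumptions. The standardised effect is 0.5 for the post value, 0.5/√[2(1 − r)] for change and 0.5/√(1 − r²) for ANCOVA. The noncentrality is that effect × √(48/2), two-sided α = 0.05.

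| r | Post value | Change score (effect) | ANCOVA (effect) |
|---|---|---|---|
| 0.3 | 67.9% | 53.6% (0.423) | 72.0% (0.524) |
| 0.4 | 67.9% | 60.0% (0.456) | 75.3% (0.546) |
| 0.5 | 67.9% | 67.9% (0.500) | 79.9% (0.577) |
| 0.6 | 67.9% | 77.4% (0.559) | 85.8% (0.625) |

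At r = 0.5 the ANCOVA variance is 0.75 of that for either t-test. This equals 1/0.75 = 1.33, or 33% more patients. Against a change score the gain shrinks as r rises: (1 + r)/2 is 0.85 at r = 0.7 and 0.90 at r = 0.8.

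**The normality switch, by simulation.** Assumptions: gamma-Poisson 72-hour counts, mean 2.5 to 3 voids per night, gamma shape 4 to 10, 48 per arm, Shapiro-Wilk at 5% in each arm as the switch. There were three scenarios, with 6,000 trials each under no effect and 3,000 each under an assumed 25% reduction.

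- t-test selected under no effect: about 5–31% of trials on post values, 63–78% on change scores.
- Type I error of the switched procedure: 4.9–5.6% on post values, 5.1–5.3% on change scores. ANCOVA with ordinary standard errors: 5.0–5.8%.
- With the 25% reduction, the t-test and Mann-Whitney on post values disagreed on significance in about 7–10% of trials.
- Power with the 25% reduction: 55–82% for the switched procedure on post values, 65–74% on change scores, 80–91% for ANCOVA.

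**The case against.** The strongest reply is that nothing here is invalid. Under randomisation an unadjusted comparison of post values or of changes is unbiased over allocations, and the switch leaves type I error close to 5%. That stands. This is a point about efficiency and about defining the effect.

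A reader might infer more in three places, and the documents do not support it:

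- *That the baseline count is thrown away.* This is true only if post values are compared. The Abstract's wording allows a change score, which uses baseline, though not efficiently.
- *That letting the data pick the test inflates false positives.* The simulation shows little sign of it. On change scores the t-test would also usually be retained.
- *That a rank test cannot give a difference with an interval.* A Hodges-Lehmann estimate can, under a location-shift model, though ties make it coarse. Section 2.12 neither promises nor excludes interval estimates, and an article may leave these to the analysis plan.

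The power figures also rest on an assumed effect and correlation, and they are normal-theory values for an outcome that may be skewed.

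It could be added that a condensed article leaves analysis detail elsewhere. That does not dispose of the point: section 2.12 states the test for continuous outcomes outright, and the article itself words the primary outcome in two ways.

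**Conclusion.** The point holds as one of precision and definition. The protocol states an unadjusted test and does not fix whether the primary variable is a post-treatment value or a reduction. Under neither version is the Week 0 count used for adjustment.

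The direction of the gain does not depend on the assumed numbers, because 1 − r² never exceeds 1 or 2(1 − r). Its size does. For r from 0.4 to 0.6 at 0.5 SD and 48 per arm, ANCOVA adds about 7 to 18 percentage points of power over a post-value t-test and about 8 to 15 over a change-score t-test. The remaining costs are uncorrected chance imbalance and an effect measure settled only after the data are seen. The change should be made, but the stated analysis would not give a biased or invalid test without it.

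**What to change.** Prespecify one primary analysis:

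- **Variable:** mean nightly voids over the 72-hour diary, worded the same way in the Abstract and section 2.8.1.
- **Time point:** one, named in advance, for example the end-of-treatment assessment at Week 3.
- **Model:** ANCOVA with treatment group and baseline mean nightly voids, with robust standard errors to deal with skew.
- **Report:** the adjusted difference in voids per night with its 95% CI.

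Use the same baseline-adjusted form for PSQI, N-QOL, TCM score, AVP and ANP. Drop the normality switch and keep Mann-Whitney as a sensitivity analysis. Covariates for diagnosis and sex are optional and not needed for this fix.

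Table 1 already schedules the baseline and follow-up measurements, so no new visits are needed. The cost is a documented amendment to the analysis text, made before unblinding.

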**Primary outcome**					
The frequency of nocturia	–	X	–	X	X

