One treatment cycle consists of 5 days of treatment followed by 2 days of rest, with 2 consecutive treatment cycles being administered. To isolate the effects of the experimental intervention, all enrolled participants (both intervention and control groups) will be instructed to refrain from receiving any additional moxibustion treatments or traditional Chinese medicine therapies (e.g., acupuncture, cupping, herbal medicine) during the 8-week study period. These restrictions were communicated verbally and in written form at enrollment. And participants will be requested to complete weekly diaries to report any inadvertent use of prohibited therapies.

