
This study aims to have a sample size of 110 patients, which will be one of the largest randomized controlled trials in this field. The target is to demonstrate the effect of HSM on nocturia in the elderly, clarify the amount of moxibustion, the distribution pattern of thermosensitive acupoints, the frequency of thermosensitive acupoints and the moxibustion sensation for the treatment of nocturia, and further clarify the regulatory effect of HSM on AVP and ANP, to provide experimental data for clarifying the therapeutic mechanism of HSM on nocturia in the elderly and direction for future basic research. Compared to previous studies (29, 30), our study boasts a shorter treatment duration, which is more readily acceptable to patients. Furthermore, our protocol places emphasis on the long-term maintenance effects of HSM, with reassessments of outcome measures conducted 2 months after treatment. Additionally, we aim to investigate the underlying regulatory mechanisms by analyzing and comparing changes in AVP and ANP levels before and after treatment. To ensure the integrity and scientific validity of the method, every step of the implementation of this clinical study will be strictly carried out, monitored and supervised.

Here are the limitations of our study: Firstly, the inclusion of only a limited number of patients as samples may restrict the representativeness and generalizability of our findings. Secondly, being a single-center study, our research may be influenced by the specific practices, patient demographics, or resource constraints of the institution, thereby limiting the broad applicability of our results. Lastly, with a follow-up period of just 2 months, our study may not adequately capture all significant clinical changes or adverse events associated with a chronic condition such as nocturia.

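### Last observation carried forward as the ITT method lets the end-of-treatment value stand in for the 2-month value, so the maintenance comparison partly assumes the lasting effect it is meant to test

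*Protocol article*

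**What the plan says.** Section 2.12 states the ITT rule outright: "missing data due to withdrawal or dropout will be handled using the last observation carried forward (LOCF) method". It then adds a fallback: "When necessary, multiple imputation methods will be considered for missing value replacement, or alternative approaches will be selected based on actual circumstances". No trigger, imputation model or role as a sensitivity analysis is attached to it. The only sensitivity analysis described there concerns prohibited therapies, not missing data.

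After the start of treatment, outcome data are collected "the day after the end of treatment and 2 months after the end of treatment". Table 1 places the primary outcome and every secondary outcome at Weeks 0, 3 and 10. Section 2.5.2 gives the treatment period: "One treatment cycle consists of 5 days of treatment followed by 2 days of rest, with 2 consecutive treatment cycles being administered". That makes 10 treatment days, followed by two months without moxibustion.

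The Discussion states what the last visit is for: "our protocol places emphasis on the long-term maintenance effects of HSM, with reassessments of outcome measures conducted 2 months after treatment". Section 2.9 allows for dropout of at most 15% and says nothing about its timing or its split between arms.

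**The concern.** Week 3 is the only scheduled outcome visit between baseline and Week 10. For anyone lost after Week 3, carrying the last observation forward puts a value from the day after treatment ended into the 2-month comparison. The method therefore assumes, for each such participant, that nothing changed over those two months. Whether the effect persists is the question the visit is meant to answer.

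If the effect fades, the 2-month group difference is pulled back towards the end-of-treatment difference and maintenance looks better than it was. The fallback does not cure this. It does not replace the stated rule, and because nothing fixes when or how it applies, the method could be chosen after the data are seen.

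**Working it through.** **Inputs from the protocol article.** 55 per arm and dropout of at most 15% (Section 2.9), which is 55 × 0.15 = 8.25, or about 8 participants per arm. Visits at Weeks 0, 3 and 10 (Table 1). A t-test for normally distributed outcomes and a significance level of 0.05 (Section 2.12), two-sided (Section 2.9). The article gives no figure for the effect of carrying values forward, so there is none to reproduce. Its sample-size figures do not depend on this point.

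**Assumptions, not in the article.** SD of 1 at each visit, correlation of 0.6 between visits, dropout at random and equal in the arms, and no change over time in the control group. D3 and D10 are the true group differences at Weeks 3 and 10, and d is the fraction lost after Week 3.

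**Step 1: expected difference at Week 10.** A fraction d contributes Week 3 values and the rest contribute Week 10 values:

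expected difference = (1 − d) × D10 + d × D3.

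**Step 2: effect fully gone by Week 10 (D10 = 0), d = 0.15.** The expected difference is 0.15 × D3. The moxibustion arm is then a mixture with variance 1 + d(1 − d)D3², and the standard error is √[(1 + d(1 − d)D3² + 1)/55]. For D3 = 1 the variance is 1 + 0.1275 = 1.1275, the standard error is √(2.1275/55) = 0.197, and the ratio of bias to standard error is 0.15/0.197 = 0.76. The two-sided rejection rate is about Φ(−1.96 + 0.76) + Φ(−1.96 − 0.76) = 0.115 + 0.003, or about 12%. The other rows follow in the same way. If half of the 15% is lost late, the late fraction is 0.075 and the other half carries baseline.

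| D3 (SD) | Apparent Week 10 difference, 15% all late | Standard error | Rejection, 15% all late | Rejection, 15% half late | Rejection, 5% all late |
|---|---|---|---|---|---|
| 0.5 | 0.075 | 0.192 | about 7% | about 5.5% | about 5% |
| 0.8 | 0.12 | 0.195 | about 9% | about 6% | about 5.5% |
| 1.0 | 0.15 | 0.197 | about 12% | about 7% | about 6% |

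Simulation under the same assumptions agrees with these rates. A t-test on the observed Week 10 values alone stays close to 5%.

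**Step 3: effect partly faded, d = 0.15 all late.** With D3 = 1.0 and D10 = 0.40: 0.85 × 0.40 + 0.15 × 1.0 = 0.49 SD reported. With D3 = 0.8 and D10 = 0.40: 0.34 + 0.12 = 0.46 SD reported.

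**Step 4: loss before Week 3.** If baseline is carried forward, a constant effect is diluted. With D3 = D10 = 0.5 and 15% early loss, the expected difference is 0.85 × 0.5 = 0.425 SD. An effect that has vanished produces no false difference. For nocturia frequency even this is unsettled: Section 2.7 records it daily during treatment, so the last observation might be an on-treatment count. The article does not say whether those counts or only the 72-hour diary of Section 2.8.1 would be carried.

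**The case against.** The strongest reply is that the problem is bounded and that the plan does not rely on carry-forward alone. Multiple imputation is already mentioned, a per-protocol analysis is planned, the primary hypothesis in Section 2.3 does not mention durability, and dropout is expected to be at most 15%. Much of this stands:

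- The bias towards maintenance comes only from loss after Week 3. With equal dropout and an effect that vanishes, it cannot exceed about 15% of D3, and the Week 3 comparison does not have it.
- Carry-forward is the stated default, not the only route open. The alternatives are discretionary, however, and the per-protocol analysis does not test the missing-data assumption.
- Durability is emphasised in the Discussion and not in the hypothesis, but Table 1 schedules the primary outcome itself at Week 10.

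Three stronger readings are tempting and are not supported:

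- **Standard errors are too small.** Each participant contributes one value to a two-sample test. With no effect at either visit, the simulated mean standard error (0.190) matches the empirical SD of the estimate (0.191), and rejection is about 5%. The excess rejection comes from bias.
- **Type I error is lost whenever the effect fades.** This holds only if the effect fades to zero. Partial fading gives an overstated estimate.
- **A false-positive rate near 23%.** That needs 15% dropout in the control arm and 25% in the moxibustion arm, a mean of 20%, which exceeds the article's own ceiling. Unequal dropout is possible because participants are not blinded (Section 2.11), but the article gives no basis for that split.

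**Conclusion.** The point holds for the 2-month comparison, and it should be fixed. The protocol article affirmatively chooses a method that assumes constancy after treatment, although it says that "our protocol places emphasis on the long-term maintenance effects of HSM". This is a stated choice and not a detail left to an analysis plan.

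Within the stated dropout ceiling the damage runs from negligible to moderate. The false-positive rate at Week 10 lies between about 5% and 12% when the effect has fully gone, and a true 0.40 SD is reported as up to 0.49 SD when D3 is 1 SD. These figures rest on assumed effect sizes, an assumed timing of loss, and random and equal dropout. If loss is mainly early, the method is more likely to dilute the effect than to inflate it. A reader might infer that the whole efficacy result is unsound, but nothing here touches the Week 3 result in that way.

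**What to change.** In Section 2.12, replace last observation carried forward as the primary ITT handling with one pre-specified method that does not assume constancy after treatment. Either of these would do:

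- a mixed model for repeated measures on Weeks 3 and 10, with baseline, arm, visit and arm-by-visit terms; or
- multiple imputation under a stated model, which also leaves room for a rank-based test if the data are not normal, as the section already foresees.

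Add one sensitivity analysis for departures from missing at random, such as a delta-adjusted or reference-based imputation. Delete "or alternative approaches will be selected based on actual circumstances". Carry-forward may stay as a labelled sensitivity analysis. If it does, state whether the daily treatment-period counts can serve as the last observation for nocturia frequency.

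The cost is a change of wording and some programming. No new data, visits or participants are needed, but the choice must be made before unblinded data are examined.
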